#### Environmental exposure

This refers to the incidental exposure of a person other than the study participant to the investigational medicinal product. This may include exposure during pregnancy and lactation if the person is exposed incidentally to the product.

#### Occupational exposure

This refers to the exposure to a medicinal product, as a result of one's professional or non-professional occupation. It does not include the exposure to one of the ingredients during the manufacturing process before the release as finished product.

The reportable events listed above may be considered potential serious breaches after consultation with the second assessor. If applicable, they will be handled as described in section 13.5.

|                                                                    |                                              |                                |
|--------------------------------------------------------------------|----------------------------------------------|--------------------------------|
| Clinical Trial Code: PROTECT
EU trial number: 2022-502332-39-00 | Trial Protocol
(Version 06; (01.10.2024)) | Page 88 of 110
CONFIDENTIAL |
|--------------------------------------------------------------------|----------------------------------------------|--------------------------------|

## 8.6 Period of Observation and Documentation

### 8.6.1 Adverse Events (AEs)

**AEs** will be ascertained by the investigators using non-leading questions, noted as spontaneously reported by the caregiver(s) of the subjects to the medical staff at any time during the trial or observed at any of the clinical trial visit.

The observational period begins with the signature of the informed consent form (ICF) and ends with the end of trial visit (V13). Same applies for SAEs/AESIs. AEs will be interrogated for at each contact between the responsible investigator and the caregiver(s) of the clinical trial subject. Thereafter, the investigator does not need to actively monitor subjects for adverse events. However, if the investigator becomes aware of a serious adverse event with a suspected causal relationship to the IMP (SAR) that occurred after the end of the observational period he or she shall report the SAE without undue delay to the Sponsor, as long as the clinical trial is still ongoing. This kind of SARs is also to be documented in the eCRF.

AEs will be documented in the subject file and in the eCRF. AEs will be reported with patient number, start and end date, description, grading, seriousness, relationship, action taken and outcome. These are the parameters that can be found on the standard AE-eCRF page. If applicable, all medical diagnoses or symptoms occurring prior to the beginning of the period of observation and documentation will be recorded in the eCRF as medical history.

The following general rules apply to the documentation of the AEs and SAEs: The start date of a SAE must not be earlier than that of the corresponding AE. The end date of a SAE is typically the same as that of the AE. The end date of the SAE must not be later than the end date of the corresponding AE. AEs and SAEs that are ongoing at the time of death are considered not resolved or resolving.

All SAEs/AESIs and their relevance for the benefit-risk assessment of the clinical trial will be evaluated continuously during the clinical trial and for the final report. All SAEs/AESIs will be documented in the eCRF and in the 'SAE/AESI Report Form' (see section 8.7.1).

### 8.6.2 Special Situations

**Special situations** (cases of medication error, misuse, overdose, use outside what is foreseen in the protocol, abuse, definitions see also chapter 8.5) shall be documented in the "Special Situation Reporting Form". All other events may only occur in a close temporal connection with the administration of the IMP. However, if a reportable event comes to the attention of the investigator with a delay, it still has to be appropriately documented and reported to the Sponsor (see section 8.7.1).

## 8.7 Investigator's Pharmacovigilance related reporting Obligations

### 8.7.1 Reporting of Serious Adverse Events, Adverse Events of Special Interest and Special Situations

All SAEs and AESIs must be reported by the investigator to the PV department of KKS Heidelberg **immediately, but not later than 24 hours after the SAE/AESI becomes known** using the 'SAE/AESI Report Form'. The initial report must be as complete as possible including details of the (serious) adverse event and an assessment of the causal relationship between the event and the IMPs.

All SAEs, AESIs are reportable to Pfizer by the PV department of KKS Heidelberg.

Exposure to the Pfizer Product such as drug overdose, medication error, occupational/environmental exposure to the Pfizer Product are reportable to Pfizer. Medication

|                                                                    |                                              |                                |
|--------------------------------------------------------------------|----------------------------------------------|--------------------------------|
| Clinical Trial Code: PROTECT
EU trial number: 2022-502332-39-00 | Trial Protocol
(Version 06; (01.10.2024)) | Page 89 of 110
CONFIDENTIAL |
|--------------------------------------------------------------------|----------------------------------------------|--------------------------------|

errors and overdoses are reportable only if associated with an SAE. Occupational/ environmental exposure is reported independently from any associated AE/SAE.

All other reportable events (see section 8.6.2) must also be reported **immediately, but not later than 24 hours after they come to the attention of the investigator** by the use of the "Special Situation Reporting Form". All available information must be included.

The reporting will be performed by faxing or e-mailing (in case of technical issues) of a completed 'SAE/AESI Report Form' / "Special Situation Reporting Form" to the PV department of KKS Heidelberg,

**[contact]**  
**or e-Mail: [contact]**

## 8.7.2 Reporting of Pregnancies

Not applicable.

## 8.8 Sponsor's Pharmacovigilance related Obligations

### 8.8.1 Sponsor's Assessment (Second Assessment)

All SAEs/AESIs will be subject to a **second assessment** by the sponsor's designated persons, who will be independent from the reporting investigator. Moreover, all other reportable events will be brought to the attention of the second assessor(s).

Despite the nature of the current trial (not blinded safety parameters are important trial endpoints), the assessor could be a study team member due to feasibility reasons and the fact that the primary endpoint is an efficacy endpoint.

The second assessor will fill out a "Second Assessment Sheet" for each SAE/AESI and send it back per fax or E-Mail to the PV department of KKS Heidelberg within 48 hours,

**fax-number: [name]**  
**or e-Mail [contact]**

The 'Second Assessment Form' will contain the following information:

- assessment of relationship between SAE/AESI and IMP(s)
- assessment of relationship between SAE/AESI and the underlying disease (trial indication)
- assessment of expectedness of SAE/AESI (derived from RSI, i.e. SmPC)
- statement if the benefit/ risk assessment for the clinical trial did change as a result of SAE/AESI.

### 8.8.2 Expedited Reporting of SUSARs

SUSARs are to be reported to the competent authorities of all member states concerned via electronic transmission to the EudraVigilance portal within defined timelines, i.e. they are subject to an expedited reporting.

The expedited reporting to the competent authorities of all member states concerned will be carried out by the PV department of KKS Heidelberg.

|                                                                    |                                              |                                |
|--------------------------------------------------------------------|----------------------------------------------|--------------------------------|
| Clinical Trial Code: PROTECT
EU trial number: 2022-502332-39-00 | Trial Protocol
(Version 06; (01.10.2024)) | Page 90 of 110
CONFIDENTIAL |
|--------------------------------------------------------------------|----------------------------------------------|--------------------------------|

The investigators will not be informed about each individual SUSAR. Instead, they will be provided with the executive summary of ASR (see section 8.8.3)

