### 1.3.10 Individual risk-benefit evaluations

In order to continuously monitor risk-benefit ratios of participants in the treatment group, the following procedures are implemented into the study visits:

1. At each study site, two subinvestigators with clinical experience in the treatment of children with TSC will evaluate the individual risk-benefit profile of the participants treated with the IMP at 6, 12, and 18 months of life, considering the individual IMP pharmacovigilance as well as possible novel findings in the research field being considered as relevant for the respective individual. These evaluations are implemented into the study visits V6, V8, and V10. If one of the evaluating pediatricians comes to the decision that the respective participant is unlikely to benefit from continuation of IMP application, the treatment will be terminated. The participant will be continued receiving SOC and will be followed-up until the primary endpoint of the study. The results from each risk-benefit evaluation will be documented in the eCRF and on a separate, signed worksheet at the respective study visit. All decisions will be reported to the coordinating investigator.
2. For independent supervision of the process, risk-benefit evaluations of the study sites will also be assessed by the DSMB within the scope of the regular meetings to minimize assessment bias risk at the study sites and to identify participants-at-risk with a comparable safety profile.
3. The coordinating investigator will continuously secure implementing novel knowledge on early prognostic factors that help to assess the individual child's risk for abnormal neurodevelopment as well as current knowledge on the risk profile of the IMP in infants. Novel findings will be shared and discussed with the Scientific Advisory Board and additionally with the DSMB and the other investigators in a timely manner.

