### 8.8.4 Annual Safety Report

Once a year an annual safety report (ASR) regarding this single trial will be prepared by the PV department of KKS Heidelberg. The main reason for preparation of a trial-specific ASR is that the Sponsor does not have a knowledge of all ongoing clinical investigations involving the IMP(s).

The international birth date (IBD) is defined as the date of first authorization to conduct the first clinical trial with the IMP in any country worldwide. In accordance with the list 'European Union Reference Dates' (EURD), the IBD applicable for this trial is 13.03.2001 (IBD for *name of IMP*).

The format of ASR will be based on the guidance on content provided in the ICH guideline E2F.

As already mentioned above, the nature of the current trial precludes insight of the Sponsor or his/her representatives in the safety data. This is especially important for data presented in a cumulative form. Therefore, ASR will be prepared by an independent second assessor(s) in cooperation with the PV department of KKS Heidelberg. The Sponsor will only be informed if any measures are required. The Sponsor will be informed by provision of the executive summary of the ASR.

In order to keep all investigators informed about the main trial-related safety findings and conclusions, they will be provided with the executive summary of ASR and with the tables/listings attached to the ASR.

Concurrently with the ASR two versions of Reference Safety Information (RSI) will be provided: i) the RSI applicable at the beginning of the reporting period and, if applicable, ii) the version submitted for approval / approved within the current reporting period.

The ASR will be submitted via EU Portal (CTIS).

|                                                                    |                                              |                                |
|--------------------------------------------------------------------|----------------------------------------------|--------------------------------|
| Clinical Trial Code: PROTECT
EU trial number: 2022-502332-39-00 | Trial Protocol
(Version 06; (01.10.2024)) | Page 91 of 110
CONFIDENTIAL |
|--------------------------------------------------------------------|----------------------------------------------|--------------------------------|

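### Site evaluators who judge each infant's risk-benefit on sirolimus have no stated route, other than yearly annual safety report material, for learning of serious related reactions at other sites

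*Protocol*

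**What the plan says.** **Information to investigators.** Section 8.8.2 (Expedited Reporting of SUSARs) says: "The investigators will not be informed about each individual SUSAR". It continues: "Instead, they will be provided with the executive summary of ASR (see section 8.8.3"). Section 8.8.3 concerns adverse reactions to auxiliary products; the ASR is described in 8.8.4. That section sets the frequency, "Once a year an annual safety report (ASR) regarding this single trial will be prepared", and says of the investigators that "they will be provided with the executive summary of ASR and with the tables/listings attached to the ASR".

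**What investigators must decide.** Under section 1.3.10 (repeated in 6.5 and 6.8), two subinvestigators at each site "will evaluate the individual risk-benefit profile of the participants treated with the IMP at 6, 12, and 18 months of life", that is, at V6, V8 and V10. The stopping trigger is a single opinion: "If one of the evaluating pediatricians comes to the decision that the respective participant is unlikely to benefit from continuation of IMP application", treatment ends. Item 3 of 1.3.10 makes the coordinating investigator responsible for keeping knowledge of the drug's risk profile in infants current, and adds: "Novel findings will be shared and discussed with the Scientific Advisory Board and additionally with the DSMB and the other investigators in a timely manner".

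**Related provisions.** Section 8.2 classifies every serious adverse reaction as unexpected. Section 8.8.4 states that "the nature of the current trial precludes insight of the Sponsor or his/her representatives in the safety data". Section 5.1.2 says that trial personnel cannot be blinded; blinding applies to the external neuropsychology observer and to the EEG, cMRI and sonography raters.

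**The concern.** The protocol places a recurring, individual safety decision with site physicians, and acknowledges in 1.3.8 that tolerability data for this drug in this age group are limited. Serious related reactions elsewhere in the trial are among the most relevant new infant data those physicians could have. Section 8.8.2 states that they are not told of these one by one, and the material that replaces individual notice is annual.

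With 17-20 sites and 60 children, about half of them on sirolimus, a site will treat few infants itself. Nearly all trial experience of serious reactions will therefore come from other sites. At stake is whether the V6, V8 and V10 evaluations use what the trial already knows. Guardians are affected too: 12.4.1 promises to inform them as soon as possible of new information that may influence participation, and a site investigator who has not heard of a reaction elsewhere cannot do so unprompted. The primary efficacy analysis is not affected.

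**Working it through.** The protocol gives no figure to reproduce. The check compares sections and then two time intervals.

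**Step 1: which events 8.8.2 covers.** A SUSAR (8.3) is a serious event that is both suspected and unexpected. Section 8.2 ends by classing every serious adverse reaction as unexpected, so on that sentence every serious reaction judged related is a SUSAR. However, 8.2 also allows reactions listed in the Reference Safety Information to count as expected, and the second-assessment form in 8.8.1 derives expectedness from it. If that document lists any serious reaction as expected, the two statements conflict and 8.8.2 covers fewer events. The reactions left over would not be SUSARs, and no route to other sites is stated for those either, apart from the ASR.

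**Step 2: the routes by which another site's reaction could reach an evaluator.**

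| Route | Section | Timing | Stated to reach other sites? |
|---|---|---|---|
| Individual SUSAR notice | 8.8.2 | none | No, expressly excluded |
| ASR summary, tables and listings | 8.8.2, 8.8.4 | yearly | Yes |
| DSMB review | 1.3.10, 12.5.1 | about six-monthly, more often if concerns arise | Not stated |
| Second assessment | 8.8.1 | within 48 hours, returned to the pharmacovigilance unit | Not stated |
| Sharing by coordinating investigator | 1.3.10 item 3 | timely | Yes, for novel findings; SUSARs not named |

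The last route is the only one that could be faster than the ASR. Section 8.8.4 leaves unclear how trial safety data would feed it, because it says the sponsor side has no insight into those data, while 8.8.1 allows a study team member to act as second assessor.

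**Step 3: timing if the ASR is the only route.** Inputs: ASR interval 12 months (8.8.4); evaluations at 6, 12 and 18 months of age (1.3.10); preparation time *p* after data cut-off, which the protocol does not give.

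- Gap between evaluations: 12 − 6 = 6 months and 18 − 12 = 6 months. Total span: 18 − 6 = 12 months.
- A reaction occurring *t* months after a cut-off reaches sites after (12 − *t*) + *p* months.
- Maximum (*t* near 0): 12 + *p* months.
- Average, if reactions fall evenly over the year: 12/2 + *p* = 6 + *p* months.
- One ASR per 12 months against a 12-month span means that, barring a report on the boundary, a new ASR falls in only one of an infant's two between-evaluation intervals. The other interval passes without one.

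A reaction just after a cut-off can thus be unknown at two evaluations of the same infant. All three are missed only if the delay exceeds 12 months and the first evaluation falls soon after the reaction.

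**Step 4: is there a blinding reason?** No. Site investigators know the allocation (5.1.2), and the blinded observer and raters need not receive the notice.

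**The case against.** The best defence is that 1.3.10 does not make other sites' SUSARs an input. Its first item points to the child's own pharmacovigilance and to new findings in the research field, the criterion is lack of expected benefit, and the promise of timeliness attaches to novel findings. That stands: a reader might infer a direct contradiction between 1.3.10 and 8.8.2, and the text does not support one.

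The protocol also has other safeguards. The DSMB reviews the sites' evaluations and looks for participants at comparable risk. Each serious event gets a second assessment within 48 hours, including whether the trial's benefit-risk has changed. Section 8.6.1 has serious events evaluated continuously, and 7.6 has investigators informed immediately of a suspension. These make it unlikely that a strong signal would wait for the ASR. They do not inform the evaluator of one infant about an individual reaction that falls short of a trial-level action.

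Four stronger readings are tempting and should not be adopted:

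- **That investigators get nothing but a summary.** Section 8.8.4 adds the tables and listings, though these are equally annual.
- **That cumulative tables ought to be kept from investigators.** The restriction in 8.8.4 concerns the sponsor and its representatives; the same section deliberately gives the tables to investigators. Removing them would leave evaluators knowing less.
- **That the coordinating investigator lacks the data.** The text leaves the route unclear, but all risk-benefit decisions are reported to that person and ASR material goes to all investigators.
- **That a reaction is typically missed at most or all evaluations.** That is the worst case in the timing above.

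**Conclusion.** The point holds as an unreconciled tension. The protocol assigns repeated individual risk-benefit decisions to site physicians and promises them timely new findings, yet tells them they will not hear of individual SUSARs and names only yearly material in place of that notice. By that route, a serious related reaction at another site may be up to 12 months old plus preparation time when it reaches the evaluators, and about 6 months plus preparation time on average.

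This rests on three assumptions: reactions spread evenly over the year (for the average only); no undocumented forwarding by the DSMB, the pharmacovigilance unit or the coordinating investigator; and the sentence in 8.2 that makes every serious reaction unexpected. The DSMB charter is a separate document and may say more. Investigators know their own site's events, so the gap concerns the other sites only.

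This is a specific and inexpensive safety improvement. It does not bear on the validity of the primary comparison.

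**What to change.** 1. In 8.8.2, replace the sentence on individual SUSARs: each SUSAR, or a short line listing, goes to all principal investigators and the DSMB at the time of expedited reporting and is on file for the V6, V8 and V10 evaluations. The blinded observer and raters are not recipients.
2. Align 8.8.2 with 8.8.4 on which ASR material investigators receive, keeping the tables and listings available to them, and correct the cross-reference from 8.8.3 to 8.8.4.
3. Reconcile the closing sentence of 8.2 with the rest of that section and with 8.8.1 on whether any serious reaction can count as expected.

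The cost is one short notice per SUSAR from the pharmacovigilance unit in a trial of 60 children, plus wording changes in 8.2, 8.8.2 and 8.8.4. Sample size, visits and analysis stay as they are.

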### 8.8.3 Reporting of Adverse Reactions of AxMP

All medicinal products defined as AxMPs in the current trial have market authorization in Germany, Austria and Switzerland. Therefore, all adverse reaction of AxMP will be reported in accordance with the applicable Medical Associations' professional codes of conduct.

### 8.8.4 Annual Safety Report

Once a year an annual safety report (ASR) regarding this single trial will be prepared by the PV department of KKS Heidelberg. The main reason for preparation of a trial-specific ASR is that the Sponsor does not have a knowledge of all ongoing clinical investigations involving the IMP(s).

The international birth date (IBD) is defined as the date of first authorization to conduct the first clinical trial with the IMP in any country worldwide. In accordance with the list 'European Union Reference Dates' (EURD), the IBD applicable for this trial is 13.03.2001 (IBD for *name of IMP*).

The format of ASR will be based on the guidance on content provided in the ICH guideline E2F.

As already mentioned above, the nature of the current trial precludes insight of the Sponsor or his/her representatives in the safety data. This is especially important for data presented in a cumulative form. Therefore, ASR will be prepared by an independent second assessor(s) in cooperation with the PV department of KKS Heidelberg. The Sponsor will only be informed if any measures are required. The Sponsor will be informed by provision of the executive summary of the ASR.

In order to keep all investigators informed about the main trial-related safety findings and conclusions, they will be provided with the executive summary of ASR and with the tables/listings attached to the ASR.

Concurrently with the ASR two versions of Reference Safety Information (RSI) will be provided: i) the RSI applicable at the beginning of the reporting period and, if applicable, ii) the version submitted for approval / approved within the current reporting period.

The ASR will be submitted via EU Portal (CTIS).

|                                                                    |                                              |                                |
|--------------------------------------------------------------------|----------------------------------------------|--------------------------------|
| Clinical Trial Code: PROTECT
EU trial number: 2022-502332-39-00 | Trial Protocol
(Version 06; (01.10.2024)) | Page 91 of 110
CONFIDENTIAL |
|--------------------------------------------------------------------|----------------------------------------------|--------------------------------|

